### Implementation evaluation

This study will use the Reach, Effectiveness, Adoption, Implementation, and Maintenance (RE-AIM) framework [74, 75] to assess the implementation of FMSPPOC among obese children. Details can be found in Table 3.

**Table 3 Tab3:** The RE-AIM framework of implementation evaluation for the FMSPPOC program

Element	Program phase	Quantitative measures	Qualitative measures
**Reach**	Pilot study	1. The number of target participants who are willing to participate in the pilot study ● 20 obese children from a weight loss center for children and adolescents in Shijiazhuang, China	1. Identify the feasibility of recruiting enough eligible participants 2. Identify the barriers for recruitment and enrolment 3. Identify the facilitators and barriers for obese children 4. Identify the reasons for participants dropout 5. Identify the strategies for improving the adherence
	Main study	1. The number of target participants who are willing to participate in the main study ● Expected: 168 obese children from six primary schools of three districts (Yu-Hua, Chang-An and Xin-Hua; two schools per district) in Shijiazhuang, China	
**Effectiveness**	Main study	1. What proportion of participants completes the intervention? ● To ensure more than 85% participants completing the intervention program	1. Explore the experience of participating in the program from participants’ views 2. Identify the conditions and circumstances that influence the intervention effectiveness 3. Identify the reasons that result in the variations/differences in the intervention effects across participants within the program 4. Identify the potential contamination for the intervention effectiveness 5. Count numbers of sports injuries and other unintended consequences during the intervention period, and analyze the reasons
		2. How do completers compare to non-completers? ● Dropout analysis will be conducted to identify the baseline difference between completers and dropouts ● Sensitivity test will be conducted to identify the impact of the dropouts on the evaluation of the intervention effects	
		3. What are the effects of the intervention on participants? ● Significant improvement in primary outcome (FMSs) and other health-related physical and psychological outcomes, e.g., PA, fitness, wellbeing, perceived motor competence and PA enjoyment (detailed outcome measures are shown in Table 4) ● Significant changes in forming a regular PA habit ● Improved awareness and knowledge on the importance of PA habit and healthy lifestyles towards FMSs and obesity prevention	
**Adoption**	Pilot study & Main study	1. The proportion of service providers/collaborators (i.e., Shijiazhuang Education Bureau, Physical Fitness Association, Lab of Measurement and Evaluation in Health Sciences and Sports Nutrition Center, Hebei Normal University, and Department of Physical Education and Research and Department of Health Care in primary schools) involved in the program ● Expected: 4 service providers/collaborators will be involved in the pilot study ● Expected: 5 service providers/collaborators will be involved in the main study 2. How about the efficiency and quality of collaboration? ● Using self-reported scale to assess the satisfaction with efficiency and quality of collaboration among different service providers/collaborators	1. Identify facilitators and barriers that affect service providers/collaborators’ participation 2. Identify the facilitators and barriers that affect the efficiency and quality of collaboration
**Implementation**	Pilot study & Main study	1. Is the intervention delivered as intended? ● Using a process evaluation framework to assess the fidelity and quality of intervention implementation (e.g., exercise intensity will be monitored during the intervention; a fidelity evaluation scale will be used) ● Trained research staff observe teachers’ implementation of the FMSPPOC program (e.g., percent of lesson content conveyed, whether lessons will be presented in recommended order) and parents’ involvement in the family-based PA assignments ● Using self-reported e-logs to assess the participants’ satisfaction with the intervention implementation ● Using a self-reported scoring sheet to assess the consistency in delivering the intervention and evaluate the consistent commitment of facilitators and collaborators	1. Identify the acceptability, adaptability, and practicality of the intervention 2. Identify any modifications that have been done during the intervention process, and explore the reasons behind them 3. Identify the barriers that influence the fidelity of the intervention 4. Identify the potential facilitators and barriers that influence the intervention implementation and provide strategies to address them in the future
		2. Did participants adhere to the intervention program? ● Analyses for the attendance rate of each session and overall completion rate ● Check the completion of the family-based PA assignment by self-reported e-logs ● Self-reported e-logs completed by the intervention facilitators and collaborators	
**Maintenance**	Main study & Follow-up	1. The extent to which the intervention outcomes are sustained ● Data analyses for the sustained intervention effects during 6-month follow-up	1. Identify the components that influence the successful sustainability of the current program 2. Identify the modifications made to sustain the current program 3. Identify the facilitators and barriers of seeking more collaborators in future 4. Identify the facilitators and barriers that maintain the program and promote the program to a wider population in future
		2. The number of participants sustained, and the number of new participants enrolled in the program ● Expected: more than 85% of participants sustained and more than 300 new participants from five main districts (60 ~ 80 participants in each district) 3. The number of PE teachers and parents have sustained their implementation of the program or disseminated the program to others ● Expected: more than 70% of PE teachers and parents sustained the implementation of the program or introduce the program to others	
		3. The degree to which the Shijiazhuang Education Bureau institutionalize the FMSPPOC as an on-going part of their regular activities (i.e., supply their own funding, integrated into programmatic activities, regularly train their staff in implementation, continue to provide data for monitoring and evaluation) ● Expected: more than 70% of service providers/collaborators continue to implement the FMSPPOC program and for at least three years	
		4. The number of new service providers/collaborators, including but not limited to NGOs, sponsorships, and local government support, join the FMSPPOC ● Expected: more than 15 new collaborators from 5 main districts (3–5 per district)	

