**Methods:**

Using a cluster randomized controlled trial (CRCT), 168 Chinese obese children (8–12 years) from 24 classes of six primary schools will be recruited and randomly assigned to one of two groups by a cluster randomization, including a 24-week FMSPPOC intervention group and a non-treatment waiting-list control group. The FMSPPOC program includes a 12-week initiation phase and a 12-week maintenance phase. School-based PA training sessions (2 sessions/week, 90 min each session) and family-based PA assignments (at least three times per week, 30 min each time) will be implemented in the initiation phase (semester time), while three 60-min offline workshops and three 60-min online webinars will be conducted in the maintenance phase (summer holiday). The implementation evaluation will be undertaken according to the RE-AIM framework. For intervention effectiveness evaluation, primary outcome (FMSs: gross motor skills, manual dexterity and balance) and secondary outcomes (health behaviors, physical fitness, perceived motor competence, perceived well-being, M-PAC components, anthropometric and body composition measures) will be collected at four time-points: at baseline, 12-week mid-intervention, 24-week post-intervention, and 6-month follow-up occasions.

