## Method

### Study design

This study will apply a two-group double-blinded cluster randomized controlled trial (CRCT) with four measurement occasions, including baseline assessment (T0), mid-intervention assessment (T1: 12 weeks after the baseline assessment), post-intervention assessment (T2: 24 weeks after the baseline assessment), and follow-up assessment (T3: 48 weeks after the baseline assessment). Two groups include: 1) an intervention group (IG), receiving the FMSPPOC intervention for 24 weeks; and 2) a waiting-list control group (WCG), receiving the FMSPPOC intervention or relevant materials (based on participants’ requirements) after the completion of all data collection for IG (see Fig. 1). The design, implementation, and reporting of the FMSPPOC will follow the SPIRIT guidelines and the CONSORT statement [54, 55] (Supplement Material 1). The study protocol was approved by the Research Ethics Committee of Hebei Normal University (ref. No.2021LLSC051). This study was a key part of a large research project funded by the National Social Sciences Funding Committee of China (Ref. No.: 19200526).

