**Additional information**	
Demographics	Children’s age, gender, grade (primaries 1–6), ethnicity (Han or others), parental educational level (below college; college or above) and yearly household income (low: RMB < 84,000; medium: RMB 84,000 – 132,000; high: RMB > 132,000) [60] will be reported by parents

In addition, the collection of all indicators at the four-time points will follow the following process. Day 1–7: Demographic information (filled by parents) and ActiGraph 3X + measured PA, sedentary behavior, and sleep; Day 8: anthropometric and body composition measures and FMSs; Day 9: physical fitness assessment; and Day 10: psychological outcomes. The Day 8–10 data collection will be implemented by four trained student helpers with assistance of PE teachers in an elementary school gymnasium, where the temperature will be constant at 20℃ and humidity will be controlled at 50% during the assessment.

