To our knowledge, FMSPPOC is the first school-family blended multi-component FMS-promotion program to be designed in China, which makes up the research and practical gaps as suggested in previous studies and shows a series of strengths: 1) standard methods will be applied for assessment of FMSs; 2) the use of theoretical framework and behavioral change techniques will ensure the implementation and effectiveness of the FMSs promotion program; 3) the gold standard for scientific designs (i.e., CRCT) will be applied and comprehensive measures will be implemented, which can contribute to a robust examination of the program effectiveness and a better understanding of the potential mechanisms; 4) the use of the RE-AIM framework will enhance the quality of the program and enable us to evaluate the implications of FMSPPOC among obese children broadly. We anticipate that FMSPPOC will also be a new paradigm of secondary obesity prevention. In addition, we will propose and assist health and education governments to advocate and disseminate the blended intervention among all primary schools to tackle unhealthy lifestyles in children and further improve health status of obese children in China. Other countries and regions with similar demographics to China can also learn and benefit from this product. Surely, comparisons to other cultures need to follow up and mechanisms are required to be evaluated, too. With that, the research of this study and comparable one can inform not only research and practice but also theory refinement and scaling up approaches.

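### Injuries are counted only within the programme's implementation evaluation and are not an outcome measured in both arms, so injury frequency cannot be compared without bias between the randomised groups

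*Protocol article*

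**What the plan says.** Table 3 (Implementation evaluation) uses the RE-AIM framework to "assess the implementation of FMSPPOC among obese children". In its Effectiveness row for the main study, the fifth item of the qualitative column reads: "Count numbers of sports injuries and other unintended consequences during the intervention period, and analyze the reasons". This is the only mention of injuries in the article. Two other items in the same cell are worded around programme participants: "Explore the experience of participating in the program" and "Identify the reasons that result in the variations/differences in the intervention effects across participants within the program".

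The outcomes measured on four occasions are listed in Table 4 (Outcome evaluation): motor skills, health behaviours, fitness, perceived competence, well-being, M-PAC components and body measures. Injury is not among them, and the Data analysis section names no injury comparison. The comparator is "a non-treatment waiting-list control group".

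The data-collection schedule after Table 4 applies at all four time points and opens with a parent-completed part: "Day 1–7: Demographic information (filled by parents".

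**The concern.** A programme that sets obese children aged 8 to 12 repeated exercise at 70–90% of maximum heart rate may cause some injuries, and children of this age are also injured without any programme. Separating the two needs injuries to be found in the same way in both randomised groups. The article lists its comparative outcomes in one table and puts injuries in another, whose purpose is to evaluate delivery of the programme.

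At stake is the balance of benefit and harm on which wider use would rest. The Discussion says the team will help health and education authorities to "disseminate the blended intervention among all primary schools". Benefit would then have a randomised estimate and injury would not. A raw programme count could be misread as harm if it is high, or as safety if it is low.

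**Working it through.** The article gives no injury rate, so there is no stated figure to reproduce. The check sets the relevant places side by side and then works through the consequence.

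**1. Channels through which an injury could surface**

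| Channel | Where described | Intervention schools | Control schools |
|---|---|---|---|
| Session attendance record | Procedure and quality control | yes | no sessions held |
| Weekly parent upload on home assignments | 12-week initiation phase | yes | no assignments set |
| E-logs from participants, facilitators and collaborators | Table 3, Implementation row | yes | nothing to log |
| Staff observation of teachers and of parents' involvement | Table 3, Implementation row | yes | nothing to observe |
| Assessments T0 to T3 | Outcome evaluation, Table 4 | yes, without an injury item | yes, without an injury item |

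The only contact described for both arms is the assessments, and those do not ask about injury.

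**2. What unequal detection does**

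Let each arm have n = 84 children, true injury risk r and detection probability s. The expected count is n × r × s, so the ratio of counts is

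(r_I / r_C) × (s_I / s_C).

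If controls are not counted, s_C = 0 and there is no ratio. If they are counted through weaker channels, s_I / s_C exceeds 1 and the ratio is biased upwards by that factor. Neither case recovers r_I / r_C.

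**3. What a programme-arm count alone can show**

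- Background injuries, assuming a 24-week risk of 5% to 20%: 0.05 × 84 = 4.2 and 0.20 × 84 = 16.8, so about 4 to 17 injured children with no programme effect.
- It does bound the absolute risk. With 0 injured of 84, the one-sided 95% upper limit is 1 − 0.05^(1/84) = 3.5%, and the 97.5% limit is 1 − 0.025^(1/84) = 4.3%. It gives no risk difference.

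**4. What a matched count would give**

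Inputs: 84 per arm and ICC 0.01 (Sample size estimate); 28 children per school, three schools per arm (Randomization and blinding). Applying that ICC to injuries within schools is an assumption. Design effect: 1 + (28 − 1) × 0.01 = 1.27. The injury risks below are assumed.

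| Risk, control v intervention | Power, 84 v 84 | Power with design effect 1.27 |
|---|---|---|
| 5% v 10% | 23% | 19% |
| 5% v 15% | 58% | 48% |
| 5% v 20% | 84% | 75% |

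(Two-sided 0.05, normal approximation for two proportions.)

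Precision for 5% v 10%: SE = √[(0.05 × 0.95 + 0.10 × 0.90)/84] = √(0.1375/84) = 0.0405, a 95% half-width of 1.96 × 0.0405 = 7.9 percentage points. With the design effect, SE = 0.0405 × √1.27 = 0.0456 and the half-width is 8.9 points. Six schools leave 4 degrees of freedom between schools; with t = 2.776 the half-width is 12.7 points.

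**5. The time window**

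School sessions and home assignments run in weeks 1–12, and workshops and webinars fill the maintenance phase to week 24. A 24-week count therefore covers all programme exposure. What it omits is the period up to the "follow-up assessment (T3: 48 weeks after the baseline assessment"), which matters only if later harms are of interest.

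**The case against.** The strongest reply is that the injury item names no arm. Its window can be read as a calendar period covering all six schools, and Table 3 is not confined to programme schools: its Reach row counts 168 children from six schools, and the contamination item in the same cell concerns the comparison between arms. The article also condenses a fuller protocol, says it follows SPIRIT and CONSORT, and foresees an operational manual. Definitions and sources for harms may well be set out elsewhere.

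This stands against any claim that control schools go uncounted. It does not remove the point. If controls are meant to be included, the channels described would still find injuries more readily where the programme is running. The criticism is of where the article puts the measure and in what form, not of detail left to another document.

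It is also fair that analysing the reasons allows case-by-case attribution, most clearly for injuries during supervised sessions, and that a count gives an absolute risk. Both stand.

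Low power is a fair objection to a hypothesis test, but not to a descriptive estimate. Equal ascertainment would also be imperfect, because families know their allocation.

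**Conclusion.** The point holds in a limited form. Injury counting is described only within the programme's implementation evaluation, with no arm named, and injury is not a two-arm outcome. On this description the trial can describe and attribute individual injuries, but cannot compare their frequency between the randomised groups without bias. The direction of bias, towards more injuries found in the programme arm, follows from the channels described. Its size cannot be known from the article, and the 4 to 17 background cases rest on an assumed risk.

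A reader might infer more, and the document does not support it:

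- **That there is no count in control schools.** This is the natural reading of the table, but it is an inference from silence.
- **That the trial cannot say whether the programme causes injuries.** This overlooks the planned analysis of reasons.
- **That home exercise is out of staff sight.** Table 3 provides for observation of parents' involvement and for e-logs.
- **That unequal injury recording undermines the dropout or per-protocol analyses.** The article gives no per-protocol definition, and its dropout analysis compares baseline differences, so this is speculation.

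This is a worthwhile, inexpensive improvement and does not affect the validity of the primary analysis.

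**What to change.** Add one fixed, identical parent-reported item to the form parents complete on Days 1–7, at T1 and T2 in all six schools: any injury since the last assessment that stopped activity for a day or more or needed medical care, with its setting. Ask it at T3 as well if harms during follow-up are of interest. T1 covers the exercise phase and T2 the maintenance phase.

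Report the item descriptively by arm for the enrolled children, with confidence intervals that allow for schools, and without a hypothesis test. Keep the Table 3 count and analysis of reasons as a supplementary description of the programme arm, labelled as such.

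Do not add an injury prompt to the weekly parent upload in one arm only. If such a prompt is used for safety detection, keep its reports out of the between-arm comparison and acknowledge that it may sharpen recall in that arm.

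The cost is one item on an existing form at two or three assessments and one descriptive table, with no extra visits. The downsides are imperfect recall over 12 weeks (about 24 at T3), parent reporting that is not blinded, and wide intervals.

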### Outcome evaluation

A description of the measurements in the present study are presented in Table 4. All the measurements will be conducted on four occasions, including baseline assessment (T0), mid-intervention assessment (T1: 12 weeks after the baseline assessment), post-intervention assessment (T2: 24 weeks after the baseline assessment), and follow-up assessment (T3: 6-month after the intervention completion).

**Table 4 Tab4:** Description of the outcome measures

Outcomes	Measurement instrument
**Primary outcome: FMSs**	
Gross motor skills	Evaluated using The Test of Gross Motor Development-Third Edition (TGMD-3) which has been validated in China with satisfied reliability [76]. The TGMD-3 includes two sub-scales, the locomotor skill sub-scale composed of six skills: run, gallop, hop, horizontal jump, slide (judged on four performance criteria) and skip (judged on three criteria), and the ball skill sub-scale (previously named object control skill in the TGMD-2) composed of seven skills: one hand forehand strike of self-bounced tennis ball, kick a stationary ball, overhand throw, underhand throw, two hand strike of a stationary ball, one hand stationary dribble and two hand catch. Before the assessment of each skill, an accurate verbal description and demonstration of each skill was carried out by a trained researcher. Each child completed three trials, one for practice and then two formal trials. Only the scores of the two formal trials were recorded for the evaluation. Children’s performances were observed and evaluated following 3 ~ 5 qualitative performance criteria for each TGMD-3 assessment skill: every criterion was scored 1 point (present) or 0 point (absent) using process-oriented checklists [77]. The total score for each item is given by the sum of both trials. Items' sums were used to calculate the score for the locomotor (46) and ball control skills sub scales (54) as well as for the overall TGMD-3 scores (100) [77]
Manual dexterity and balance	Assessed using a subscale of the Movement Assessment Battery for Children-Second Edition (MABC-2, band 2 and 3) [78], which has demonstrated good reliability and validity in Chinese children [79]. Manual dexterity, which is composed of placing pegs, threading lace and drawing trail 2. Balance, which includes one-board balance, walking heel-to-toe forwards and hopping on mats. The scoring was consistent with the method published in the movement ABC-2 UK manual [78]
**Secondary outcomes**	
Health behaviors: PA, sedentary behavior, and sleep	The ActiGraph GT3X + accelerometer (ActiGraph LLC, Pensacola, FL, USA) will be used to objectively monitor whole-day PA. All participants will be asked to wear a monitor at the waist on an elasticized belt at the right midaxillary line. Participants were encouraged to wear the accelerometer 24 h per day (removing only for water-based activities: i.e., swimming/bathing) for at least 7 d, including two weekend days. Days with > 16 h/d of activity recordings (from midnight to midnight) were considered as valid [80], and the minimum amount of non-sleep data that was considered acceptable for inclusion was at least 4 days with at least 10 h of wake wear time per day, including at least one weekend day [81]. Data were collected at a sampling rate of 80 Hz downloaded in 1-s epochs with the low-frequency extension filter using the ActiLife software version 6.13 (ActiGraph LLC) and reintegrated to 15-s epochs for analysis. Non-wear time will be defined as a period of 20 consecutive minutes or more zero counts [82]. Night sleep duration was calculated in R software using GGIR package (version 2.0) default algorithm, as described by Van Hees et al. [83]. Evenson cut-off points [82] will be applied to determine non-sleep time spent in light (25–574 counts/15-s), moderate (574–1003 counts/15-s) and vigorous PA (> 1003 counts/15-s), and total sedentary time as all movement ≤ 25 counts per 15 s. Parents will be instructed to fill in sleep logs for their child with the purpose of cross-validating the waking (wear) time
Physical fitness	Assessed using the revised 2014 version of the Chinese National Student Physical Fitness Standard (CNSPFS) [84], involving a total of 11 physical fitness indicators. The 7 described below are suitable for primary school students, including BMI, vital capacity, 50 m sprint, Sit and reach, timed skipping rope, timed sit-ups (just Grades 3–6) and 50 m × 8 shuttle-run (just Grades 5 and 6). Following the guidelines, test examiners conducted each test per a protocol determined a priori. Each fitness indicator score was weighted by a grade- and sex-specific percentage
Perceived motor competence	Assessed using the subscale (athletic competence) of the Self-perception Profile for Children (SPPC) [85]. Athletic competence subscale of SPPC includes 6 items, three of the items are worded such that the first part of the statement reflects low competence or adequacy, and three are worded to first reflect high perceptions of competence or adequacy. This counterbalancing is reflected in the scoring of items, where half of the items are scored 1, 2, 3, 4 and half are scored 4, 3, 2, 1. This is to insure that children are tracking the content of the items and are not simply providing random response choices or are always checking the same side of all questions. In addition, the Chinese version of the SPPC has adequate reliability, ranging from 0.61 to 0.76 [86]. The structure and criterion validity are acceptable [87]
Perceived well-being	The Chinese version of the 12-item Psychological Well-Being Scale for Children (PWB-C) will be used [88, 89]. PWB-C contains six dimensions of psychological well-being: environmental mastery, personal growth, purpose in life, self-acceptance, autonomy, and positive relations with others. Options were given on a 4-point Likert scale, ranging from 1 (“almost never”) to 4 (“very frequently”). The mean score of the 12 items will be calculated, with a higher score indicating a higher level of perceived well-being
M-PAC components of PA for both parents and children	The Chinese translated items of M-PAC components of PA will be used [90–92]. The questionnaire package includes measures for behavioral intention, instrumental and affective attitudes, perceived capability, perceived opportunity, parental support (intentional and actual), action planning and coping planning, action control, habit strength, and identity. The response options and scoring approach will be consistent with the settings in previous studies [65, 66, 90, 91]
Anthropometric and body composition measures	Height and weight will be measured calibrated medical digital scales (RGT-140, Changzhou, China) and portable stadiometer (GMCS-I, Beijing, China) to the closest 0.05 kg and 0.1 cm, respectively following a standardized protocol [84]. Waist circumference will be measured using a flexible plastic tape at 1 cm above the umbilicus from the horizontal level in a standing position, at the end of a normal expiration [92]. Each of aforementioned anthropometric indexes was measured twice and the mean value was used for data analysis. A Bio-Impedance Analysis (BIA) was conducted using Portable body composition analyzer (InBody230, Seoul, South Korea) and Lokin Body 120 software (DMS-BIA technology; InBody Co., Seoul, South Korea) to estimate body composition, including percent of body fat (PBF), fat mass (FM), fat-free mass (FFM, kg) and skeletal muscle mass (SMM, kg). The instrument was validated against dual-energy X-ray absorptiometry for school-age children with satisfactory results for estimating body fat [93]
